### Number of participants required

From the Cambridge proof-of-concept pilot study using non-specialist screeners, the sensitivity is assumed to be 70% and 95% for red-reflex and digital imaging screening by non-specialist staff respectively. Hence the treatment effect is assumed to be a 25% difference. Power calculations need further assumptions regarding the joint distribution of the test within individual babies; we assume the maximum rate, 35%, of discordant tests consistent with these margins. A 2-sided hypothesis test (McNemar’s) at the 2.5% significance level will have 90% power if 67 babies are recruited with cataracts, necessitating recruitment of 140,000 newborns for screening.

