## Abstract

**Background:**

Congenital cataract is the commonest cause of preventable child blindness in the world. It affects 1: 3000 babies, 60% of whom will have bilateral disease. Although screening of the newborn red-reflex with an ophthalmoscope is recommended, there are questions over this technique's accuracy, particularly in non-specialist hands. Several studies in enriched paediatric eye clinic populations have demonstrated superior accuracy when a digital image of the the eye's reflection to infrared light is evaluated.

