**Methods:**

140,000 newborn babies will be recruited into the study from at least 13 maternity units in England over an 18 month period. Babies will have both the standard red-reflex assessment and evaluation of the infrared-reflex using a prototype device. Since specialist gold-standard evaluation of every participant is impractical, bespoke data linkage requests to NHS England will be made. Data from the red-reflex evaluation and the presence of codes relating to cataract diagnosis and/or treatment in Hospital Episode Statistics (HES) will be retrieved for each participant a minimum of 6 months after their birth. This data will be used to calculate relative and absolute sensitivity and specificity for each screening test and comparison of accuracy using the McNemar test. Secondary outcome measures will include comparison of accuracy in different ethnic groups and screener usability scores.

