### Procedure to account for missing or spurious data

Participants in whom the S4N or the neocam dataset are missing will be excluded from statistical analysis. Where the quality of scans is insufficient when reviewed by the assigned paediatric ophthalmologist evaluator, the site will receive additional training.

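### At the article's own prevalence of 1 in 3,000, 140,000 babies yield about 47 cataracts, not 67, and power for sensitivity is about 74%, not 90%

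*Protocol article*

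**What the plan says.** In the Protocol article, the section on the number of participants required sizes the study on the sensitivity contrast:

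- Sensitivities: "the sensitivity is assumed to be 70% and 95% for red-reflex and digital imaging screening by non-specialist staff respectively".
- Effect: "Hence the treatment effect is assumed to be a 25% difference".
- Discordance: "we assume the maximum rate, 35%, of discordant tests consistent with these margins".
- Test: "A 2-sided hypothesis test (McNemar’s) at the 2.5% significance level".
- Result: the test "will have 90% power if 67 babies are recruited with cataracts, necessitating recruitment of 140,000 newborns for screening".

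That section gives no prevalence. The only one in the article is in the Abstract, Background: "It affects 1: 3000 babies, 60% of whom will have bilateral disease". The Abstract, Methods, repeats the target: "140,000 newborn babies will be recruited into the study from at least 13 maternity units in England over an 18 month period". On incomplete records, the section on missing or spurious data says: "Participants in whom the S4N or the neocam dataset are missing will be excluded from statistical analysis". It gives no expected rate of such exclusions and no inflation of the target.

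**The concern.** The sample size rests on two steps: from power to the number of cataract babies, and from that number to the number of newborns. The second step needs a prevalence. When the printed prevalence is applied to the printed recruitment target, it gives roughly 47 cataracts, about 30% fewer than the 67 on which the 90% power depends.

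Sensitivity is one of the two primary contrasts and the one that the study is sized on. If the yield is 47, the chance of missing a true 25-point gain is about 26% by the exact test, not 10%. A non-significant result could then be read as evidence against the device when the study was too small to settle the question. The findings are to go to the UK National Screening Committee, so that misreading would matter.

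**Working it through.** **Inputs.** All come from the article: sensitivities 70% and 95%, difference 0.25, discordance 0.35, two-sided alpha 0.025, target 140,000 (all from the sample size section) and prevalence 1 in 3,000 (Abstract, Background).

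**Step 1. Discordant cells.** Maximum discordance under the margins is (1 − 0.70) + (1 − 0.95) = 0.35. With difference 0.25, the cells are:

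- digital imaging positive only: (0.35 + 0.25) / 2 = 0.30
- red-reflex positive only: (0.35 − 0.25) / 2 = 0.05

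**Step 2. Reproduce the 67.** For the exact McNemar test, sum over the number of discordant pairs m:

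Power(n) = Σ over m of Bin(m; n, 0.35) × P(two-sided binomial test on m pairs gives p ≤ 0.025), with a share 0.30 / 0.35 = 0.857 of discordant pairs favouring digital imaging.

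- n = 66: 89.8%
- n = 67: 90.4%

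So 67 is the smallest n at which exact power reaches 90%, which agrees with the article. The usual normal (Connor) formula gives nearly the same:

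n = [2.241 × √0.35 + 1.282 × √(0.35 − 0.25²)]² / 0.25² = (1.326 + 0.687)² / 0.0625 = 64.8, so 65.

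**Step 3. From cataracts to newborns.**

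- Expected yield: 140,000 / 3,000 = 46.7
- Newborns needed for 67: 67 × 3,000 = 201,000
- Prevalence implied by 67 in 140,000: 140,000 / 67 = 2,090, so about 1 in 2,090 (3,000 / 2,090 = 1.44, or 44% higher than printed)

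If the count is Poisson with mean 46.7, the chance of 67 or more cataracts is about 0.3%.

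**Step 4. Power at the expected yield.**

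| Calculation | n = 67 | n = 47 |
|---|---|---|
| Exact McNemar | 90.4% | 74.1% |
| Continuity-corrected | 90.2% | 71.4% |
| Normal approximation (Connor) | 91.0% | 76.5% |
| Asymptotic or mid-p | 93.2% | 80.4% |
| Miettinen | 94.6% | 80.7% |

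The exact test is the like-for-like comparison because it gives 67 as the smallest n for 90%. Averaged over Poisson variation around 46.7, exact power is 73%.

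**Step 5. Could eyes explain the gap?** With 60% bilateral disease, 46.7 × 1.6 = 75 eyes, which is not 67. The sample size section also counts babies, and the statistical method section analyses one index eye per baby.

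**Step 6. Exclusions.** The article gives no rate, so these are assumptions. Losing 5%, 10% or 15% of babies leaves about 44, 42 or 40 cataracts, with exact power of 70%, 68% or 65%.

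**The case against.** The strongest reply is that the power statement is conditional on 67 cataracts and is correct on that condition. The 1 in 3,000 is a round background figure, not labelled as a planning input, and the full protocol may hold a different one. At 1 in 2,000, for instance, 140,000 babies give 70 cataracts, enough for 67 with about 4% to spare. This is possible, and it means the cause of the mismatch cannot be known from the article. It does not remove the mismatch: the article says that 67 cataracts require 140,000 newborns while printing a prevalence under which they require 201,000.

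A second reply is that 35% discordance is the worst case for power under the stated sensitivities. This is true. At 47 cataracts, exact power would be 85% at 30% discordance and 97% at the 25% minimum. But 35% is the article's own planning basis, and its 90% with 67 rests on it. The minimum would mean that digital imaging misses no cataract that red-reflex examination finds, which is a different and unstated assumption.

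Third, the withdrawal section says that losses from withdrawn consent would be made up by further recruitment. That stands for withdrawals, but it does not extend to babies excluded for missing screening data.

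Finally, the planned confidence intervals for the difference give a careful reader some protection against over-reading a null result, and the specificity contrast does not depend on the cataract count. Both points are fair. Neither corrects the stated power for sensitivity.

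**Conclusion.** The concern holds. The step from 67 cataracts to 90% power is right; the step from 67 cataracts to 140,000 newborns contradicts the only prevalence that the article gives. On that prevalence, the target yields about 47 cataracts, 20 fewer than planned, and power for the primary sensitivity contrast is about 74% by the exact test (71% to 81% across versions of the calculation), before any exclusions for missing data.

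This rests on the article's own 70% and 95% sensitivities, 35% discordance and two-sided 2.5% level, and on 1 in 3,000 applying to the recruited babies. If the planners used a prevalence near 1 in 2,090 or higher, the 90% may stand, but then that figure must be stated and supported.

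**What to change.** In the sample size section, state the prevalence used and make it agree with the Abstract. One of two changes is needed:

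1. Keep 1 in 3,000 and restate the design: 140,000 newborns give about 47 expected cataracts and about 74% power (exact McNemar, two-sided 2.5%, 35% discordance), before exclusions.
2. Keep 67 cataracts and 90% power, and state and justify the prevalence of about 1 in 2,090 that this requires with no losses (higher if losses are allowed for). Use that prevalence throughout.

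In either case, say what allowance, if any, is made for babies excluded because a screening record is missing.

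Both changes are wording only and need no extra babies; the cost of the first is a less favourable stated power. Keeping 90% power at 1 in 3,000 would instead mean a target of 201,000, which is 61,000 more newborns, and is not needed to correct the text. The article reports that the study still awaits regulatory approval before site training, so the correction can be made before recruitment starts.

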### Criteria for the premature termination of the trial

Poor image quality on reviewed images which is due to technical device issues rather than user error may result in a temporary suspension of the trial in one or all sites to modify the device.

### Procedure to account for missing or spurious data

Participants in whom the S4N or the neocam dataset are missing will be excluded from statistical analysis. Where the quality of scans is insufficient when reviewed by the assigned paediatric ophthalmologist evaluator, the site will receive additional training.

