## Introduction

### Background and rationale

Congenital cataract is the commonest cause of avoidable childhood blindness worldwide
^
1–
3
^. Red-reflex screening for congenital cataract is recommended by the UK National Screening Committee within 72 hours of birth and at 6–8 weeks as part of the Newborn and Infant Physical Examination (NIPE). Early surgery for severe cataract is time critical, being required within the first months of life to prevent permanent visual deprivation amblyopia.

Screeners report finding red-reflex assessment difficult because of their unfamiliarity both with rare eye conditions and the technique of ophthalmoscopy
^
4
^. Additionally, darker ocular pigmentation and the baby’s pupil constriction and aversion reflexes to bright light can limit the quality of the assessment
^
5–
8
^. A national surveillance study found that only 60% of children having cataract surgery before the age of two years had been referred via the NIPE screening programme
^
9
^. Conversely, audit data record that referrals to specialist clinics for possible red-reflex abnormalities are 10 times the frequency expected for the prevalence of the condition (Public Health England audit data 2019).

Recent studies have indicated that screener evaluation of the infrared (IR)-reflex image using a prototype camera is superior in accuracy to standard red-reflex assessment in cataract enriched childhood cohorts
^
10,
11
^. If confirmed in a population screening setting, a more accurate test could minimise the number of babies with cataract whose diagnosis is delayed due to a false negative assessment and reduce the number of unnecessary false positive referrals to specialist clinics and the parental anxiety that causes.

The aim of this study is to confirm or refute the hypothesis that the sensitivity and specificity of screening with IR digital imaging using the neocam prototype device is superior to the standard ophthalmoscopic red-reflex test. This study will provide data for a subsequent health economic analysis to establish if replacing the standard method of screening with IR digital imaging would be cost effective in terms of health outcomes and reduction in unnecessary referrals.

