## Objectives and outcome measures

### Primary objective

To estimate and compare the sensitivity and specificity of screening evaluation with the standard test to the intervention digital imaging test in newborn babies.

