### The intervention

After registration, the neocam device is used to image the IR-reflex in each eye. This procedure will be undertaken by a screener who has attended site training, but NIPE and Good Clinical Practice (GCP) certification is not obligatory. The imaging should take place in in either the cot or in the parent’s arms in a normally lit room.

The IR LED illuminates automatically after each eye is selected on the device display. The screener visualises the eye through the device display and aligns a visible ring calliper on the display with the corneal limbus of each eye to promote imaging at an optimal distance. The screener first evaluates the quality of the image (for movement blur and eye closure) and retakes the image if necessary. Imaging will generally take less than 2 minutes in total. Subsequently the screener evaluates each image as “normal” or “abnormality suspected” on the keypad when prompted by the device user interface. This evaluation is stored in the image file name. This ends the baby’s active participation in the study.

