### Withdrawal of participants from the study

**
*Prior to registration.*
** This will include babies whose parents do not assent and those without an assigned NHS number. Additionally, if there are insufficient staff to undertake the study intervention or if the device is not working. In all cases, the reason for withdrawal following parent consent will be entered in the study database.

**
*Following registration.*
** Parents may withdraw their consent for data linkage or the use of the images in future development work by contacting the central research team. The reason for withdrawal reason, if given, will be documented on the eCRF in the trial database.

The data and images for registered babies in whom consent has been withdrawn will be retained in the study database and only event data up to the withdrawal date will be collected via data linkage. Given the absence of risk and the single use of the intervention, these numbers are not predicted to be high but further recruitment would be required to replace their loss.

**
*Usability and screening preference feedback from screeners.*
** Screeners undertaking either the standard red-reflex test or neocam imaging will attend site training prior to clinical use. Each will be asked to complete an anonymised usability questionnaire
^
12
^ during the study period.

**
*Definition of the end of the trial.*
** The end of trial will be 6 months after the last data capture via data linkage.

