## Statistics and data analysis plan

### Statistical method

Given the rarity of cataract, and to maximise the data from eyes with cataract captured in the study, the abnormal eye will be selected as the index eye for data analysis where there is a unilateral abnormal screening result. Where the screening test is abnormal bilaterally, the right eye will be selected as the index eye.

A comparison of the relative sensitivity and specificity of the two tests will be possible using the counts of discordant pairs of screening tests, where one, and only one, of the neocam and standard test results within a baby are positive. Thus this relative comparison will be estimable in a short space of time for the recruited population using the expert image review as the gold standard. Hence much of the statistical inference can be performed before the long-term follow-up of the babies with both tests as negative.

For both the groups with and without congenital cataracts (as determined by the gold standard) the sensitivity and specificity, respectively, will be compared. McNemar’s test will provide a p-value, and a 2-sided 2.5% significance level used to account for the two contrasts. The absolute difference and odds ratios will also be estimated and provide with 95% confidence intervals. 

An estimate of the absolute values of, rather than differences between, sensitivity and specificity will be made following TSC expert review of the neocam images of babies with double negative screening tests in whom diagnostic and / or procedure codes indicating cataract were retrieved from HES on data linkage (since the cataract may have developed after birth). A detailed statistical analysis plan will be produced before the final database lock or before any interim analysis is performed.

Equivalent comparisons of sensitivity and specificity for each screening test will be made within ethnic groups and screener experience levels.

Quantitative comparison of the ease of the standard screening examination to the intervention will be analysed by screener questionnaire at the end of that staff member’s rotation on the maternity ward or at the end of the study recruitment period, whichever is sooner
^
12
^. Summary statistics reporting on the numerical or categorical questions will be provided.

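### The missing-data rule does not separate failed screening tests from lost data, and a small imbalance in failures could cancel the specificity advantage

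*Protocol article*

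**What the plan says.** All references are to the protocol article.

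- *Procedure to account for missing or spurious data* sets the rule: "Participants in whom the S4N or the neocam dataset are missing will be excluded from statistical analysis". It makes no exception and gives no companion analysis. The next sentence deals with poor images by training alone: "Where the quality of scans is insufficient when reviewed by the assigned paediatric ophthalmologist evaluator, the site will receive additional training".
- *Registration* and *The intervention* place registration on the device before imaging. *The intervention* foresees poor images: "The screener first evaluates the quality of the image (for movement blur and eye closure) and retakes the image if necessary". It does not say what is recorded if the retake also fails.
- The result is binary: "Subsequently the screener evaluates each image as “normal” or “abnormality suspected” on the keypad when prompted by the device user interface". *Primary outcome measure* gives the same two categories for both tests, and neither has a category for a result that could not be obtained.
- *Withdrawal of participants from the study* covers babies who leave before registration, including "if there are insufficient staff to undertake the study intervention or if the device is not working". Those reasons are entered in the study database.
- *Primary objective* covers both measures: "To estimate and compare the sensitivity and specificity of screening evaluation with the standard test to the intervention digital imaging test in newborn babies". *Statistical method* tests both: "McNemar’s test will provide a p-value, and a 2-sided 2.5% significance level used to account for the two contrasts".

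**The concern.** Missing data can arise in two different ways. An S4N record that does not link, a lost upload or a withdrawn consent says little about how either test performs. A test that was attempted and gave nothing evaluable, because of eye closure, blur or an unobtainable reflex, is part of how that test performs. The stated rule treats both alike and discards both.

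If failed attempts are stored as missing, the McNemar contrasts describe only babies in whom both tests worked. *Background and rationale* gives reduction of unnecessary referrals as a purpose of the study, and a difference in failure rates bears on that directly. The same section says that pigmentation, pupil constriction and aversion to light limit red-reflex quality. Failure may therefore depend on the eye and on ethnicity, which is a secondary comparison.

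The specificity contrast is the more exposed of the two. Red-reflex false positives are already rare, so the most that neocam can gain is small.

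**Working it through.** **Inputs from the article**
- Prevalence: 1 in 3,000 (*Abstract*).
- Red-reflex referrals: "referrals to specialist clinics for possible red-reflex abnormalities are 10 times the frequency expected for the prevalence of the condition" (*Background and rationale*).
- Sensitivity 70% for red reflex and 95% for neocam, 35% discordant, 67 cataracts, 140,000 babies, 90% power (*Number of participants required*).
- McNemar's test, two-sided 2.5% (*Statistical method*).

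**Assumed, because the article does not give them**
- Neocam false-positive rate q: 0 to 0.2%.
- Failure rates f (neocam) and g (red reflex): up to 5%.
- The two tests are independent within babies without cataract.

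**The plan's own figure.** n = (z₀.₉₈₇₅·√0.35 + z₀.₉₀·√(0.35 − 0.25²))² / 0.25² = 64.8, so 65. Exact McNemar power at 67 is 90.4%. The stated 67 is reproduced.

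**Room for a specificity gain.** Red-reflex positives are 10/3,000 of all babies, of which 0.70/3,000 are true positives. The false-positive rate is p = (10 − 0.70)/(3,000 − 1) = 9.3/2,999 = 0.31%. Among 140,000 × 2,999/3,000 = 139,953 babies without cataract this is about 434. A perfect neocam could gain no more than this 0.31 percentage points.

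**Failures counted as positive.** Neocam specificity becomes (1 − q)(1 − f) and red-reflex specificity (1 − p)(1 − g). With g = 0 they are equal at f = (p − q)/(1 − q):

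| Neocam false-positive rate q | Break-even f | Babies |
|---|---|---|
| 0 | 0.31% | 434 |
| 0.1% | 0.21% | 294 |
| 0.2% | 0.11% | 154 |

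With g above zero, the break-even is close to f − g = p − q. What matters is the excess of neocam failures over red-reflex failures.

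McNemar z at q = 0.1% (positive values favour neocam; the critical value is about 2.24):

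| f | g | Complete case | Failures as positive | Failures as normal |
|---|---|---|---|---|
| 1% | 0 | +12.2 | −24.9 | +12.4 |
| 1% | 1% | +12.2 | +5.0 | +12.2 |
| 2% | 1% | +12.1 | −16.2 | +12.3 |
| 1% | 2% | +12.1 | +24.6 | +12.1 |

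First row in counts:
- Complete case: 429 red-reflex-only and 138 neocam-only false positives, z = (429 − 138)/√567 = +12.2.
- Failures as positive: the neocam positive rate is 0.001 × 0.99 + 0.01 = 1.099%. Neocam-only positives are 139,953 × 0.01099 × 0.9969 = 1,533, and z = (429 − 1,533)/√1,962 = −24.9.

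**Sensitivity.**
- Failures as normal: 0.95 × 0.95 = 0.9025, about 90.3%, if 5% of cataract babies fail imaging; 0.95 × 0.90 = 85.5% if 10% fail.
- Failures as positive: sensitivity rises, 0.95 × 0.95 + 0.05 = 95.25% at 5%.

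**Power.** By the normal approximation, power is 91.0% with 67 cataracts. It is 89.4% after a 5% loss (63.7 left) and 87.4% after a 10% loss (60.3 left).

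**The case against.** The strongest reply is that the article never says a failed image is a missing dataset. Each image is keyed as one of two results and the result is stored in the file name, so a poor image that has been keyed is not missing. Poor quality has its own sentence, which leads to training and not to exclusion. S4N holds evaluation codes, and nothing says that an unobtainable reflex leaves them empty. This stands: whether failures are excluded depends on an unstated recording rule, so the point is conditional. It does not remove the point, because the article gives no outcome for a retake that fails and its exclusion rule has no qualifier.

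A reader might infer that the rule will reverse the specificity result or flatter neocam. The article does not support that. Reversal needs failures to count as positive and neocam to fail more often than red reflex. With equal 1% failure neocam keeps its advantage, and with failures counted as normal specificity does not reverse. No failure rate is given for either test. Nor does the article say that a failed test leads to referral; a repeated test is not a referral.

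A reader might also infer that exclusion favours the more failure-prone test on both contrasts. It does not under a single convention: counting failures as positive lowers that test's specificity but raises its sensitivity. For the same reason, making failures positive in the primary analysis would be a debatable choice.

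Two practical objections also stand in part. Babies without a usable image cannot be classified by expert image review, so their disease status must come from HES. Failure rates and supplementary analyses could be left to the promised statistical analysis plan, but the exclusion rule is already fixed here, and a plan that followed it would inherit the problem.

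**Conclusion.** The point holds in conditional form. The rule merges attempted tests that gave no evaluable result with data lost for unrelated reasons, and excludes both. If failures are stored as missing, both primary contrasts apply only to babies who could be tested.

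The specificity margin implied by the article is at most about 0.31 percentage points. A net excess of neocam failures of about 0.1% to 0.3% of babies, counted as positive, would cancel it, and a larger excess would reverse it. Counted as normal, the cost falls on sensitivity instead.

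These sizes rest on assumed failure rates, an assumed neocam false-positive rate and independence of the two tests. The direction is unknown. The rule should be amended before recruitment, but nothing here shows that the trial's conclusion would be wrong.

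**What to change.** - Amend *Procedure to account for missing or spurious data* so that exclusion applies only where a test was not attempted, or where its data were lost or withdrawn.
- Record an attempted-but-not-obtainable outcome for neocam in the study database, alongside the reasons already entered there under *Withdrawal of participants from the study*. This needs no change to the device software. For red reflex, use the S4N evaluation codes where they distinguish this outcome, and say so where they do not.
- Report the failure rate for each test, by cataract status and by ethnicity.
- Beside the complete-case result, pre-specify an analysis that retains failed tests, once as screen-positive and once as screen-negative. Use the same rule for both tests, and take disease status from HES for babies without a usable image.

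The cost is a little extra data entry and analysis, and the test with more failures will look less favourable on specificity or on sensitivity. *Study status* says that site training has not begun, so the timing is good. Later it would be harder: saved records cannot be edited and images are deleted from the device after upload, so failures that were never coded may not be recoverable.
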